### Statistical analyses

The primary outcome measures are the physical functioning sub-scale of the SF-36 and the knee-specific instrument. The trial is pragmatic in design and therefore the primary analysis will be 'by intention to treat' in that all participants properly randomised will be included in the analysis even if they do not receive the intervention they were allocated to receive. A secondary analysis will be limited to participants who received the treatment to which they were randomised.

Data were collected at four time points: baseline, six, twelve, and 24 months. We shall use PROC, the mixed model procedure in the Statistical Analysis System (SAS), to analyse the data from all four time points within a single model and to adjust for experimental site. This model is robust to data missing at random and can also take the covariance structure of the data into account [43]. We shall check that the data fulfil the assumptions of the mixed model. If the data are not missing at random we shall seek an alternative analytical method providing a better fit. We shall treat missing items within individual outcome measures according to the instructions for that measure. For each outcome measure we shall calculate the number of non-responders and compare the proportion and type of non-response in each group at each time point. We shall also check that the model is a good fit and transform the data if necessary to improve fit.

The secondary outcome measures are the other seven subscales of the SF-36, the EQ-5D itself, the number of days patients take off work for their knee problems, and the number of days they are prevented from doing normal activities by their knee problems. The EQ-5D and the other seven subscales of the SF-36 will be analysed the same way as the primary outcome measures. As the number of days off work or normal activities is likely to follow a skewed distribution we shall transform the data and present the median and inter-quartile ranges for these times.

Secondary analysis of the primary outcome measures will be performed to adjust for the variation in waiting times between GP referral and access to MRI or orthopaedic specialist. Further analyses will test whether variables such as age and sex affect patient outcome, and to compare findings between different types of knee injuries (e.g. meniscal or ligamentous). As this analysis will not have the same power as the trial as a whole it will generate hypothesis rather than test them definitively.

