### Interventions

#### Direct access to MRI (experimental intervention)

At each hospital, imaging was performed with standard commercially available MR imagers using imaging protocols at the discretion of the radiologist. 'Excess treatment costs' were used to ensure that participants in the experimental group could have early access to MRI within twelve weeks of referral from their GP, who then used the MRI findings to inform diagnosis and plan subsequent management. Participants with normal MRI findings received treatment including advice to return to normal activities, undertake quadriceps exercises, and referral for physiotherapy depending on their clinical history. GPs were advised that when radiologists reported a serious abnormality like a tumour on an MRI examination the participant should be fast-tracked as normal.

To avoid contaminating our evaluation by differences in waiting times between the two clinical policies, we asked GPs to make a provisional referral to orthopaedics at the same time as requesting MRI. This was to ensure that the total waiting time from GP consultation to orthopaedic appointment was similar for both trial arms. Thus the trial will establish the more appropriate sequence of events rather than try to assess the influence of variations in waiting times.

There is evidence that educational interventions to support the dissemination of clinical guidelines can improve GPs' knowledge of MRI use [26] and the routine attachment of educational messages to radiologists' reports can avoid unnecessary GP referral [27]. We therefore delivered educational seminars to GPs about MRI, clinical diagnosis and conservative management and attached the educational message shown in Figure 2 to the radiologists' reports.

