#### Referral to orthopaedic specialist in secondary care (the control intervention)

The potential delay between GP referral and a participant's outpatient appointment with an orthopaedic specialist varied across experimental sites from three to eighteen months. We therefore used 'excess service support costs' when necessary to run extra clinics to reduce the waiting time for an orthopaedic appointment from GP referral to within nine months, and the delay between orthopaedic consultation and arthroscopy to within nine months. Reducing the waiting time from GP referral to arthroscopy to eighteen months meant that following up participants for two years would ensure the evaluation covered most relevant events including arthroscopy. Orthopaedic specialists decided whether to request MRI as normal.

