#### Referral process

To measure 'diagnostic and therapeutic impact' of direct access to MRI, we asked GPs to complete a pre-randomisation questionnaire that recorded their diagnosis, management plans and confidence therein [42]. We asked them to complete a similar questionnaire on receipt of the imaging report or orthopaedic specialist letter. We also record the patient waiting times from randomisation to MRI, orthopaedic consultation, and arthroscopy. Adherence to the referral process is one of the outcomes of interest rather than a factor that may jeopardise interpretation of the findings.

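### The secondary analysis limited to participants who received their allocated treatment is open to selection bias; a complier-average estimate would be a better adherence analysis

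*Protocol article*

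**What the plan says.** All places are in the Protocol article.

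- **Statistical analyses.** The primary analysis is by intention to treat: "all participants properly randomised will be included in the analysis even if they do not receive the intervention they were allocated to receive." The next sentence adds: "A secondary analysis will be limited to participants who received the treatment to which they were randomised."
- **Referral process.** "Adherence to the referral process is one of the outcomes of interest rather than a factor that may jeopardise interpretation of the findings." The waits from randomisation to MRI, orthopaedic consultation and arthroscopy are recorded.
- **Direct access to MRI.** Extra funding was used so that "participants in the experimental group could have early access to MRI within twelve weeks of referral from their GP." A provisional orthopaedic referral was made alongside the MRI request, so that "the total waiting time from GP consultation to orthopaedic appointment was similar for both trial arms."
- **Referral to orthopaedic specialist.** Extra clinics were run where needed to "reduce the waiting time for an orthopaedic appointment from GP referral to within nine months." Before that, waits varied by site from three to eighteen months. Specialists could request MRI as they normally would.
- **Outcome measures.** Questionnaires are sent at six, twelve and 24 months after allocation.

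**The concern.** Restricting a randomised comparison to those who received their allocation conditions on something that happens after randomisation. The two groups that remain need not be comparable. Three features of this trial add to that general weakness.

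1. If receipt means attending, the qualifying event is an MRI in one arm and a specialist appointment in the other, and the ceilings on the wait differ widely. The provisional referral equalises the wait to the orthopaedic appointment. It does not equalise the wait to the step that would define receipt.
2. A control who waits more than six months reports the six-month outcome before the event that decides inclusion. A good outcome could then be the reason for not attending.
3. The Referral process section treats adherence as a result of the referral policy. The restricted analysis uses that result to select participants.

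At stake is a secondary estimate that could differ from the intention-to-treat result through selection alone and be taken for the effect of the care when delivered.

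**Working it through.** **The plan's own figure.** Inputs from the Sample size section: SD 25, difference 6.75 points (0.27 SD), 5% significance, 80% power.

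n per arm = 2 × (1.96 + 0.84)² × 25² / 6.75², which rounds up to 216 with unrounded normal quantiles. The plan has 217, which gives 80.3% power. The figure reproduces as two-sided (one-sided would need 170), so 6.75 points and 217 per arm serve as the yardstick.

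**The waits.** Nine months = 9 × 52/12 = 39 weeks, and 39/12 = 3.25. The control ceiling is therefore about 3.25 times the MRI ceiling. These are ceilings, not observed waits. A site with a three-month orthopaedic wait (3 × 52/12 = 13 weeks) would be about level with the MRI ceiling.

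**Bias of the restricted comparison with no true effect.** Let q be the share of an arm that does not receive its allocated step, and d the amount by which non-receivers score better than receivers, in SDs. The mean of receivers lies q × d × SD below the mean of the whole arm. Hence

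bias (MRI minus control) = 25 × (q_control × d_control − q_MRI × d_MRI).

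The documents give no value of q or d, so every input below is an assumption. With q_MRI = 5% and the same d in both arms:

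| d (SD) | q_control | Bias (points) | Type I error |
|---|---|---|---|
| +0.5 | 10% | 25 × 0.05 × 0.5 = +0.6 | 5.7% |
| +0.5 | 20% | 25 × 0.15 × 0.5 = +1.9 | 11% |
| +0.5 | 30% | 25 × 0.25 × 0.5 = +3.1 | 22% |
| +1.0 | 10% | 25 × 0.05 × 1.0 = +1.3 | 7.9% |
| +1.0 | 20% | 25 × 0.15 × 1.0 = +3.8 | 31% |
| +1.0 | 30% | 25 × 0.25 × 1.0 = +6.3 | 65% |
| any | 5% (equal) | 0 | 5% |
| −0.5 | 20% | 25 × 0.15 × (−0.5) = −1.9 | 11% |

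Type I error is for a simple two-sided comparison of means with 217 × (1 − q) per arm. The ends of the range are illustrations, not limits: −0.5 SD paired with 30% control non-receipt would give −3.1.

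**Do the planned adjustments remove it?** Adjusting for site and including baseline in the mixed model do not capture recovery during the wait. The separate secondary analysis that adjusts for waiting time uses another post-randomisation variable tied to arm, so it does not restore comparability either.

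**The alternative.** Complier-average effect = intention-to-treat difference / difference between arms in receipt of early MRI. If no control has MRI before a specialist consultation, an intention-to-treat difference of 6.75 becomes 6.75/0.95 = 7.1, 6.75/0.90 = 7.5 or 6.75/0.80 = 8.4 points at 5%, 10% or 20% non-receipt in the MRI arm. The interval widens by about the same factor, and the test is essentially the intention-to-treat test.

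**The case against.** **Receipt is not defined in the article.** The Trial design section describes both interventions as referrals. If receipt means being referred, the longer opportunity to recover and not attend largely disappears. This stands as a condition on the point. The missing definition is no fault in itself, since a condensed article may leave it to the analysis plan.

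**The direction is not established.** A reader might infer that the analysis necessarily retains sicker controls and so favours MRI. The documents do not support that: they give no attendance rates, reasons for non-attendance or outcomes of non-attenders. The bias vanishes when the arms match, and it reverses if non-receivers do worse, for example because they were treated elsewhere.

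**The size can be overstated.** Counting only control losses gives larger figures: 20% non-receipt with a 20-point gap shifts the control mean by 4.0 points, 59% of 6.75. That sets MRI-arm loss to zero, which nothing in the article supports.

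**The analysis is secondary.** Intention to treat is primary, and the recorded waits would show differences between arms. This stands, and it limits the importance of the point.

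**The alternative answers another question.** A complier-average estimate with early MRI as the treatment rescales the intention-to-treat effect. It does not compare delivered MRI with delivered consultation. This also stands and belongs with the costs.

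None of this removes the remaining weakness: if receipt means attendance, the article commits to a comparison that selects on a post-randomisation event whose timing may differ by arm.

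**Conclusion.** The point holds as a cheap improvement to a secondary analysis. The restriction is open to selection bias, plausibly but not certainly favouring MRI. In the scenarios shown the bias is about −1.9 to +6.3 points, or −28% to +93% of the 6.75-point target (1.9/6.75; 6.25/6.75), and it is zero when non-receipt and relative recovery are the same in both arms. The size rests wholly on assumed values of q and d, and on receipt meaning attendance.

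Two stronger readings should be resisted. One is that the trial's main conclusion is at risk; the intention-to-treat analysis does not depend on receipt. The other is that the plan contradicts itself by naming adherence as an outcome and then restricting on it. The two statements sit uneasily together, but an analysis labelled secondary is not ruled out by the first.

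**What to change.** In Statistical analyses, make a complier-average causal effect estimate the preferred adherence analysis:

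- Use random allocation as the instrument.
- Define receipt as MRI before any specialist consultation, so that MRI requested by a specialist for a control does not count.
- Adjust for baseline score and the stratification factors (site, distance to hospital, number of partners).
- State the exclusion restriction, that allocation acts only through early MRI. It is plausible because MRI-arm participants who do not attend still hold the provisional orthopaedic referral, but it cannot be tested.
- State monotonicity, that nobody would have early MRI only if allocated to control. It needs stating in case some controls obtain early MRI.

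Report receipt by arm. Keep the restricted analysis, if at all, as descriptive, with a note of its likely selection bias.

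The cost is a sentence or two and one two-stage model, using waits to MRI and consultation that are already recorded. The downsides are a wider interval (about 1/0.90 = 1.11 times at a 90% difference in receipt), untestable assumptions and no gain in power over intention to treat. The estimate also describes early MRI among compliers rather than delivered MRI against delivered consultation.

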### Sample size

A similar group of patients followed up six months after referral for MRI of the knee had a mean of 64 and standard deviation (SD) of 25 on the physical functioning sub-scale of the SF-36 [37]. Hence a trial that followed up 434 participants (217 direct access and 217 controls) would have 80% power using a 5% significance level to identify a standardised difference of 0.27, equivalent to 6.75 points on the SF-36 physical sub-scale or an analogous difference on the proposed knee-specific instrument. We judge that a standardised difference of 0.27 in either of these measures should be clinically important. As we estimated that we could achieve 85% response rates to postal questionnaires, we aimed to recruit 500 participants in all.

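### The primary mixed model pools the pre-randomisation baseline with the follow-ups, does not condition on it, and names no primary contrast to which the stated 80% power belongs

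*Protocol article*

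**What the plan says.** The Statistical analyses section of the protocol article states: "Data were collected at four time points: baseline, six, twelve, and 24 months". It then plans a SAS mixed model "to analyse the data from all four time points within a single model", adjusting for experimental site. It mentions no baseline covariate, no treatment-by-time term and no contrast. The two primary outcomes, SF-36 physical functioning and the trial's own knee instrument, carry no time point. The Outcome measures section places the baseline questionnaire before randomisation.

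The Sample size section says that 434 followed-up participants, 217 per arm, "would have 80% power using a 5% significance level to identify a standardised difference of 0.27", which is "equivalent to 6.75 points on the SF-36 physical sub-scale or an analogous difference on the proposed knee-specific instrument". The SD comes from an outside group who, "followed up six months after referral for MRI of the knee had a mean of 64 and standard deviation (SD) of 25". The section does not say that six months is the primary time.

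The section on the control intervention says extra clinics were used to bring "the waiting time for an orthopaedic appointment from GP referral to within nine months", with up to nine further months to arthroscopy. It gives this as the reason for following participants for two years.

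**The concern.** Baseline precedes allocation, so the true difference between arms at that point is zero. If baseline enters the model as one of four equivalent responses, the result depends on which term is reported:

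- A treatment effect averaged over all four points includes one point where nothing can differ.
- A contrast at one follow-up, with arm means left free at baseline, leaves the baseline score unused.
- A change-from-baseline contrast uses baseline, but less efficiently than adjustment does.

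The article's own sections also point to different times. The SD comes from six months, while the length of follow-up is justified by events up to 24 months. The differences at 6, 12 and 24 months need not be equal. With two primary outcomes and no contrast fixed, the headline estimate could be chosen after the data are seen, and the power statement cannot be matched to the test that will be made.

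**Working it through.** **Inputs from the article.** Difference 6.75 points, SD 25, 217 per arm, 5% significance (taken as two-sided, which reproduces the stated figure), four time points, baseline before randomisation.

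**Assumptions not in the article.** The true difference is 6.75 points at 6, 12 and 24 months. The SD is 25 at every time. Data are complete. Any two times have the same correlation ρ (compound symmetry), shown for ρ = 0.3, 0.5 and 0.7.

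**Step 1: the plan's own figure.** n per arm = 2 × (1.960 + 0.842)² × (25/6.75)² = 215.3, rounded up to 216, against the stated 217. At 217 per arm the standard error is 25 × √(2/217) = 2.400. Power is Φ(6.75/2.400 − 1.96) = 80.3%, or 80.1% by the noncentral t. The stated figure is therefore right for one two-sample comparison at one time, without baseline.

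**Step 2: dilution if all four points are averaged equally.** Expected effect = (0 + 6.75 + 6.75 + 6.75)/4 = 5.06 points, or 0.2025 SD, which is 25% below 6.75. The weights depend on the covariance structure. With a single common treatment effect and first-order autoregressive correlation of 0.5, generalised least squares gives baseline a weight of one third, and the expected effect is 4.50 points.

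**Step 3: power by contrast.** Power = Φ(effect / (2.400 × √v) − 1.96), where v is the variance of the contrast in units of SD².

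| Contrast | Effect (points) | v | ρ = 0.3 | ρ = 0.5 | ρ = 0.7 |
|---|---|---|---|---|---|
| One follow-up, baseline unused | 6.75 | 1 | 80% | 80% | 80% |
| Equal average of all four points | 5.06 | (1 + 3ρ)/4 | 86% | 76% | 67% |
| Change from baseline to one follow-up | 6.75 | 2 − 2ρ | 66% | 80% | 95% |
| One follow-up, baseline as covariate or arms constrained equal | 6.75 | 1 − ρ² | 84% | 90% | 98% |
| Mean of three follow-ups, baseline unused | 6.75 | (1 + 2ρ)/3 | 97% | 93% | 88% |
| Mean of three follow-ups, baseline as covariate | 6.75 | (1 + 2ρ)/3 − ρ² | 99% | 99% | >99% |

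Example at ρ = 0.5, one follow-up with baseline as covariate: v = 0.75, standard error 2.400 × 0.866 = 2.078, and power Φ(3.248 − 1.96) = 90%.

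**Step 4: where the four-point average loses power.** Averaging lowers the variance as well as the effect. Power equals 80% when √v = 5.0625/(2.400 × 2.802) = 0.753, so v = 0.567 and ρ = 0.42. It is below 80% only for larger ρ.

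**Step 5: adjustment against its alternatives.** 1 − ρ² never exceeds 1. Also (2 − 2ρ) − (1 − ρ²) = (1 − ρ)², which is never negative. At a single follow-up, conditioning on baseline is therefore never less precise than ignoring it or taking the change score, whatever ρ is.

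**The case against.** The best defence is that the sentence is compressed. A model with baseline as a covariate also uses data from all four time points, as does one that keeps baseline as a response with arms constrained equal. Neither dilutes anything. Model terms are commonly left to an analysis plan, and none is shown here. This stands in part: the article does not call baseline a response in so many words and does not say that a pooled main effect will be reported. Having baseline among the responses is not itself an error.

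A reader might infer more in three places, and the article does not support it:

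- **That the trial's estimate is diluted by a quarter.** This needs a pooled effect without interaction, equal weights and a constant follow-up difference, all together. A diluted effect is also not the same as lost power (step 4).
- **That the 80% power belongs to no comparison at all.** The Sample size section defines a two-group difference, and it reproduces. What is missing is its time point and its link to the mixed model.
- **That many controls are still unseen at six months.** The article gives maximum waits, not a distribution. It also takes steps to make orthopaedic waits similar in the two arms and plans a secondary analysis adjusted for waiting time.

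Most of the contrasts in the table meet or exceed the design power, so the case for adjustment is largely one of efficiency. What remains is that the article does set out its primary model, and what it sets out lists baseline beside the follow-ups, adjusts for site alone and identifies no estimate.

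**Conclusion.** The point holds in a limited form. The described model leaves the handling of baseline open and ties neither primary outcome to a time point or contrast. The 80% power is arithmetically correct for one time, but is attached to no estimate from that model.

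The 25% dilution is a risk that the wording permits and not a feature of the plan as stated. The more dependable gain is in precision: at a single follow-up, baseline adjustment adds about 4, 10 and 17 percentage points of power at ρ of 0.3, 0.5 and 0.7 (80.3% to 83.8%, 90.1% and 97.6%). These sizes rest on compound symmetry, complete data, equal SDs and an assumed ρ. That adjustment is no less precise at a single time holds for any ρ when the SDs are equal.

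**What to change.** - Model the 6, 12 and 24 month scores with the baseline score as a covariate, or keep baseline as a response with arm means constrained equal there. Include treatment, time, treatment-by-time and site.
- Name one post-baseline contrast, excluding baseline, as the source of the primary estimate for each primary outcome, and report the others as secondary.
- State in the sample size section which contrast the 80% refers to. It can be kept as a conservative figure that takes no credit for baseline.

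The choice of contrast is the sponsor's. The 24-month difference fits the stated reason for two-year follow-up. However, the abridged telephone form offered at the last 24-month reminder holds only the EQ-5D and five knee items, so SF-36 physical functioning would be missing for those who use it. The mean of the three follow-ups is another candidate if an average over two years is the quantity of interest.

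The cost is a few sentences, settled before the outcome data are examined by arm. The baseline scores are already collected, so no new data are needed.

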#### Randomisation

When a participant completed the baseline questionnaire a designated member of the practice phoned the remote randomisation service at the University of York Trials Unit for the random allocation. They then informed the participant of their allocation and the GP made the appropriate referrals. As the trial was pragmatic in design, so as to reflect the consequences of routine GP access to MRI, blinding of participants or professionals to treatment allocation was not appropriate.

The randomisation service ensured immediate and unbiased allocation of individual participants between the two arms of the trial. The service recorded information to identify all participants and their eligibility. There is evidence of substantial inter-observer variability in radiologist reporting of MRI of the knee [29]; there is also evidence that practice list size [30] and distance from general practice to MRI centre [31] influence referral for MRI. We therefore stratified the randomisation procedure by experimental site, median distance from practice to hospital, and median number of partners in practices as a proxy for practice list size. Within strata a block allocation sequence was used; permuted random blocks of size 2 or 4 were randomly selected to generate the allocation sequence.

When the trial began we recruited participants from practices in Hull and East Yorkshire, York and North Yorkshire, Grampian and North Wales. Delays, for example in the approval of NHS costs from North Wales, led us to extend this invitation to practices to participate in Lothian, Bradford, Rotherham, Sheffield and Tayside. We modified the randomisation procedure for practices from these sites to reduce administration and expedite recruitment. The new procedure required the GP to establish eligibility, obtain consent, make the orthopaedic referral, and provide the participant with the baseline questionnaire and contact details form. The participant posted completed forms to York where the Trial Secretary entered the data into the randomisation database, performed the randomisation, and posted the results of the allocation to the GP and the participant.

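### Randomisation is stratified by site, distance and number of partners, but the primary model names adjustment for site alone; a minor mismatch that may cost a little precision

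*Protocol article*

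**What the plan says.** In the Randomisation section the protocol article says the trial team "stratified the randomisation procedure by experimental site, median distance from practice to hospital, and median number of partners in practices", the last serving as a proxy for list size. Within strata, "permuted random blocks of size 2 or 4 were randomly selected to generate the allocation sequence". The reason given for the two practice-level factors is that "practice list size [30] and distance from general practice to MRI centre [31] influence referral for MRI". That is a statement about referral. The article does not say that either factor predicts SF-36 physical functioning or the knee-specific score.

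In the Statistical analyses section, the mixed model for both primary outcomes is to "analyse the data from all four time points within a single model and to adjust for experimental site". The EQ-5D and the other seven SF-36 subscales are to be handled in the same way. Distance and number of partners are not mentioned in that section, and no reason is given for leaving them out.

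**The concern.** Blocking within strata forces the arms to be nearly balanced on every stratification factor. Any outcome variation due to those factors is therefore largely removed from the real sampling error of the treatment difference. A model without the factors does not know this: it leaves that variation in the residual and reports a standard error that reflects it. Confidence intervals are then wider than they need be and p-values somewhat too large.

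Here one of the three design factors is carried into the analysis and two are not. At stake is a modest amount of precision for both primary outcomes and for the secondary outcomes that share the model. Validity is not at stake.

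**Working it through.** **Inputs from the Sample size section.** The reference group "had a mean of 64 and standard deviation (SD) of 25 on the physical functioning sub-scale of the SF-36". The trial "would have 80% power using a 5% significance level to identify a standardised difference of 0.27", "equivalent to 6.75 points on the SF-36 physical sub-scale", with 217 followed up per arm. Sidedness is not stated; two-sided is assumed.

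**Input not in the document.** R² is the share of outcome variance explained by distance and number of partners beyond site. It is varied over 0%, 2%, 5% and 10%.

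**Step 1: reproduce the plan's figure.** The normal approximation, n = 2(1.960 + 0.842)² / 0.27², gives 216 per arm after rounding up. The t-test solution is 216.3, which rounds up to the plan's 217. Power at 217 per arm is 80.3% (normal) or 80.1% (t-test). The stated 434 stands, and it does not rely on any covariate.

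**Step 2: standard errors.** A model without the two factors reports about SE = 25 × √(2/217) = 2.400 points. Under stratified allocation the actual standard error is 2.400 × √(1 − R²), which is also about what the full model reports.

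**Step 3: power and type I error**, with Δ = 6.75.
- Site-only power = 1 − Φ((1.960 × 2.400 − Δ) / actual SE)
- Full-model power = Φ(Δ / actual SE − 1.960)
- Site-only type I error = 2(1 − Φ(1.960 × 2.400 / actual SE))

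| Assumed R² | Actual SE | SE overstated by | Power, site only | Power, all three factors | Type I error, site only |
|---|---|---|---|---|---|
| 0% | 2.400 | 0% | 80.3% | 80.3% | 5.0% |
| 2% | 2.376 | 1.0% | 80.5% | 81.1% | 4.8% |
| 5% | 2.339 | 2.6% | 80.9% | 82.3% | 4.4% |
| 10% | 2.277 | 5.4% | 81.6% | 84.2% | 3.9% |

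**Step 4: check by simulation.** The set-up was 434 participants, nine sites (the four initial and five added sites in the Randomisation section), two binary practice factors, blocks of 2 or 4, one follow-up, and 4000 runs per scenario. Power for site only against all factors was 79.95 vs 79.9% at R² = 0, 80.2 vs 80.6% at 2%, 80.2 vs 81.3% at 5% and 80.7 vs 83.5% at 10%. At R² = 10% the site-only model reported an SE of 2.40 while its estimates had an SD of 2.26. Simulated site-only type I error was 4.9, 5.2, 5.0 and 4.3%. The Monte Carlo standard error is about √(0.05 × 0.95 / 4000) = 0.34 points, so only the 10% case is visibly below nominal.

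**Step 5: allow for baseline.** The planned model includes the baseline score. As a simplification, treat baseline as a covariate, with correlation 0.5 between baseline and follow-up and equal stratum effects at both times (both assumed).
- Site-only reported SE: 2.400 × √(1 − 0.5²) = 2.078
- All-factor SE: 2.400 × √[(1 − R²) − (0.5 − R²)² / (1 − R²)] = 2.071, 2.060 and 2.040 at R² = 2%, 5% and 10%

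The site-only SE then exceeds the all-factor SE by 0.3%, 0.9% and 1.9%, about a third of the excess without baseline. A simulation on the same assumptions with 425 participants gave power of 89.6 vs 89.7%, 89.8 vs 90.3% and 89.8 vs 90.7%.

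**The case against.** The strongest reply has three parts.

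1. **The consequence is conditional.** A reader might infer that the site-only model's standard errors are certainly too wide and that power is certainly lost. The document does not support that. It ties distance and list size to referral for MRI and nowhere to the outcomes; if they are not prognostic within site, the two models perform alike. This part stands in full.

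2. **The planned model may already absorb most of the effect.** Practice-level factors that shift scores at follow-up would plausibly shift them at baseline too, and baseline is in the model. This stands as a reason to expect a smaller gain. How much smaller depends on a correlation that the article does not give.

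3. **A one-sentence model description in an article need not list every covariate,** and it does not say that site is the sole one. This stands only in part. The article does name an adjustment, and what it names is one of its own three stratification factors. That is a stated choice that departs from the stated design, not silence left for an analysis plan to fill. If the full plan already includes all three factors, the correction is one of wording.

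It would also go too far to say that the benefit of stratifying is thrown away. Site, the factor placed beside the evidence on variability in radiologists' reporting, is adjusted for.

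**Conclusion.** The mismatch between the Randomisation and Statistical analyses sections is real but minor. Its direction is certain and its size is not: omitting prognostic stratification factors can only make the reported standard error too large, and omitting non-prognostic ones does no harm. On a single follow-up without baseline, adding the two factors gains nothing at R² = 0, about 0.5 points of power at 2%, 1.4 points at 5% and 2.7 points at 10%. With baseline in the model the gain is probably smaller.

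A reader might infer a threat to the planned 80% power or to the type I error rate. Neither follows: at the planned 217 per arm, site-only power stays at about 80% or above in every scenario, and the test is at worst conservative. These results rest on the assumed R² range, a two-sided 5% test and, for the baseline step, the assumed correlation of 0.5.

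**What to change.** Enter above/below-median distance and above/below-median number of partners as fixed effects alongside site in the primary mixed model, and in the EQ-5D and remaining SF-36 subscale analyses that follow it. If the factors are to stay out, say why.

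The cost is two binary covariates, that is, two degrees of freedom among more than 400 participants. Both factors were used for allocation, so they should be on record for every participant and need no new data collection. The sample size does not change.
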